### Intervention

The hUC-MSCs produced by Ever Union Biotechnology Co. Ltd. (EUBIO) are transported to the ward on the infusion day. The hUC-MSCs are suspended in 0.9% normal saline. In addition to inspecting the quality of the hUC-MSC product by EUBIO, the staff of the Stem-cell Center in CHCMU will confirm the viability and quality of the hUC-MSC product before the infusion.

There is currently no effective therapy for BPD patients, who are often given traditional supportive treatments such as nutritional support, fluid restriction, and respiratory support (including ventilator support and oxygen supply) so all participants will be given traditional supportive treatments to ensure their safety. Thus, the intervention groups will be given the traditional supportive treatments and extra low- or high-dose hUC-MSC infusion and the control group will be given only the traditional supportive treatment. Participants will be unable to use glucocorticoids 3 days before or after the hUC-MSC treatment.

A total of 72 patients in the intervention groups will be randomized in a 1:1:1 pattern to receive low-dose hUC-MSCs (*n* = 24; 2.5 million cells/kg) or high-dose hUC-MSCs (*n* = 24; 5 million cells/kg) in combination with traditional supportive treatments or traditional supportive treatments alone (*n* = 24).

### Withdrawal

Discontinuation may occur due to participant death, severe adverse effects (SAEs), other serious disease-limiting participation, or study withdrawal requested by the guardian. If the participant withdraws from the trial, the reason for the withdrawal and all the results of observations will recorded in detail. Meanwhile, a new participant will be enrolled in the trial to replace the withdrawn subject.

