### Adverse events

AEs are defined as adverse medical events that occur after the subjects or their guardians provide written informed consent until the end of the study visit. AEs include abnormal laboratory results, symptoms, or diseases. All AEs will be recorded on a Case Report Form (CRF) and the researcher should provide comprehensive clinical reports. Once AEs occur, we will follow the principle of “the first priority of the participants,” take the necessary treatment according to the patients’ specific situation, and decide whether to suspend the clinical research. The main investigator should immediately inform the Scientific Research Office, Medical Service, and Ethics Committee of CHCMU. The SAE report should be submitted in writing within 24 h, while a follow-up SAE report should be submitted to the Human Research Ethics Committee.

An insurance policy will be prepared for all participants, who will be provided with ancillary and post-trial care in the case of injury or death as a result of their participation in the trial.

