### Outcome evaluation

The outcome measures and their time frames of this trial are listed in Table 3. The primary endpoint is the cumulative duration of oxygen therapy, i.e., the duration from starting to stopping oxygen treatment.

**Table 3 Tab3:** Outcome measures

Measures			Time frames
Primary outcomes	Cumulative duration of oxygen therapy		Until the time of stopping oxygen therapy
Secondary outcomes	Adverse events	Number of serious adverse events	Within 24 h post hUC-MSCs infusion
		Acute infusion associated adverse events	From the start of the trials to 1 month post hUC-MSCs infusion
		Late infusion associated adverse events	Within 2 years post hUC-MSCs infusion
	The rate of supplemental oxygen therapy		At 1 month post hUC-MSCs infusion
	Duration of invasive mechanical ventilation		
	Duration of noninvasive mechanical ventilation		
	The first time of stopping oxygen supplement		
	The rate of re-oxygen supplement		
	Pulmonary function changes		At 6, 12, and 24 months post hUC-MSCs infusion
	Chest radiography changes		
	Blood oxygen saturation		At 1, 3, 6, 12, and 24 months post hUC-MSCs infusion
	Mortality		
	Times of hospital readmissions		
	Complications of preterm birth		

The secondary endpoints include the safety and efficacy outcomes. The safety of the study will be assessed by the number of AEs including SAEs, acute infusion-associated AEs (AIA-AEs) and late infusion-associated AEs (LIA-AEs). SAEs include death, any malignant cardiac event (new ventricular tachycardia, ventricular fibrillation, or asystole, cardiac arrest), acute pulmonary embolism, stroke, anaphylactic shock, acute transplant rejection, and any other diseases extending the hospital stay. AIA-AEs include fever, general allergic reaction (rash, edema, erythema, pallor), infection at the injection site, vital sign changes, laboratory test changes (indicators of liver and kidney function, cardiac markers, indicators of hematology and immunity, markers of hepatitis/syphilis/HIV/tuberculosis, and urinalysis). LIA-AEs include tumorigenic events (tumor formation) and teratogenic events.

The efficacy endpoints are as follows: duration of oxygen therapy, duration of invasive mechanical ventilation, duration of noninvasive mechanical ventilation, the first time stopping the supplemental oxygen, rate of re-oxygen supplement, blood oxygen saturation, chest radiography changes, pulmonary function changes, mortality, number of hospital readmissions, and preterm birth complications.

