### Statistical analysis

SPSS version 17 (SPSS Inc., Chicago, IL, USA) statistical analysis software will be used to analyze the data in the study. Significant differences will be considered at an α level of 0.05.

The data will be examined at group assignment to the intervention and control groups using the *χ*^2^ test, *t* test or analysis of variance (ANOVA). For the intervention and control groups, the indicators at baseline and at 1 day, 3 days, 7 days, 1 month, 3 months, 6 months, 12 months, and 24 months will be compared with repeated measures ANOVA. Comparison of these outcome indicators including duration of oxygen therapy, duration of mechanical ventilation, pulmonary function tests, and quantitative scores of chest radiography changes between the intervention and control groups will be conducted using the *t* test. Mortality and hospital readmission rates will be tested by the *χ*^2^ test, while 24-month mortality will be analyzed by Kaplan-Meier curves.

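### The withdrawal rule lets infants leave the trial after a serious adverse event without keeping them in follow-up, so the 24-month Kaplan-Meier mortality would be biased low if they leave

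*Protocol article*

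**What the plan says.** The Withdrawal section of the protocol article gives the reasons for stopping: "Discontinuation may occur due to participant death, severe adverse effects (SAEs), other serious disease-limiting participation, or study withdrawal requested by the guardian". It continues: "If the participant withdraws from the trial, the reason for the withdrawal and all the results of observations will recorded in detail", and adds that "a new participant will be enrolled in the trial to replace the withdrawn subject". It does not say whether a withdrawn infant is still contacted for survival or adverse events.

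Four other parts of the article bear on this:

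- **Study objectives:** the first objective is long-term safety and efficacy.
- **Outcome evaluation, Table 3:** mortality is assessed up to 24 months, and late infusion-associated adverse events up to 2 years. The SAE list is wide and ends with "anaphylactic shock, acute transplant rejection, and any other diseases extending the hospital stay".
- **Table 2 and Follow-up procedures:** contacts are at 1, 3, 6, 12 and 24 months, with adverse events and mortality marked at each. No exception is made for infants who have had an SAE.
- **Statistical analysis:** "24-month mortality will be analyzed by Kaplan-Meier curves".

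**The concern.** In this trial an SAE is both a safety outcome and a permitted reason to stop observing the infant. Table 2 marks the cell infusion only in the screening and baseline columns, and controls receive none. For an SAE after that point there is no study infusion left to stop, so discontinuation most naturally means leaving the study. The section heading and the replacement sentence support that reading.

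Kaplan-Meier estimation assumes that censored infants have the same later risk of death as those still followed. An infant censored at an SAE probably has a higher risk, so the curve would understate mortality. The trial is open-label and exit is discretionary, so the understatement can differ by arm. If one dose raised the SAE rate and its infants left more often, its mortality curve would be flattered most. Replacement adds to the problem: if the infant who left is dropped from the analysis set, the randomised comparison is altered and that infant's later death is not counted.

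**Working it through.** **Figures in the plan.** The article states no SAE rate, no share of infants leaving after an SAE, no mortality after an SAE and no expected bias, so there is no figure of its own to reproduce on this point. The sample size (21 per group, 24 after 10% loss, 72 in total) does reproduce for a 13-day difference with SD 15, two-sided alpha 0.05 and 80% power. This point does not affect it.

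**Inputs**

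- True 24-month mortality M = 41%, the severe-BPD figure in Background. The article gives no time horizon for it; 24 months is assumed. The overall-BPD figure of about 15% is used as a low case.
- Share of infants with an SAE: f = 20% (assumed).
- Probability of death after an SAE: p = 50%, 60% or 80% (assumed).
- Share of SAE infants who leave: q = 0, 50% or 100% (assumed).
- Timing (assumed): SAEs uniform over 0 to 12 months, death after an SAE with an exponential lag of mean 2 months, other deaths uniform over 24 months.

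**Step 1: mortality in infants without an SAE.** Overall mortality is fixed at M, so the remaining infants die with probability

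p0 = (M − f × p) / (1 − f)

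- p = 50%: (0.41 − 0.10) / 0.80 = 38.8%
- p = 60%: (0.41 − 0.12) / 0.80 = 36.3%
- p = 80%: (0.41 − 0.16) / 0.80 = 31.3%

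If every SAE infant is censored at the SAE, the only deaths left to observe are in this group. The Kaplan-Meier value then falls to about p0. It is slightly lower still, because in this model SAE infants add time at risk but no deaths before their SAE.

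**Step 2: Kaplan-Meier value at 24 months** (simulated, M = 41%, f = 20%)

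| Death after an SAE | None leave | Half leave | All leave |
|---|---|---|---|
| 50% | 41% | 39.3% | 37.3% |
| 60% | 41% | 38.1% | 34.8% |
| 80% | 41% | 35.9% | 30.0% |

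**Step 3: other settings.** With p = 80% and all SAE infants leaving, f = 10%, 20%, 30% and 40% give 36%, 30%, 23% and 13%. With M = 15%, f = 20%, p = 40% and all leaving, the estimate is about 8%.

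**Step 4: a second model.** Here the SAE occurs at month 1 and multiplies the hazard of death afterwards. With f = 20% and a hazard ratio of 3, a true 41% is estimated as 37.8% if half leave and 33.8% if all leave; a true 15% becomes 13.4% and 11.3%. With a hazard ratio of 1, or with nobody censored, the bias is zero.

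**Step 5: comparison with sampling error.** The standard error for 24 infants is √(0.41 × 0.59 / 24) = 0.100, or 10 points. In the Step 2 table the bias runs from 41 − 39.3 = 1.7 points (about 0.2 standard errors) to 41 − 30 = 11 points (about 1.1 standard errors).

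**The case against.** A reader might infer that the sickest infants will leave follow-up and that the mortality curve is biased low as a matter of fact. The article does not support that:

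- The Withdrawal section says discontinuation may occur. It does not say that an SAE must lead to exit, or that vital status is no longer collected after exit. Observations on withdrawn infants are recorded, the Adverse events section requires a follow-up SAE report, and the follow-up schedule carries no exception.
- Leaving the study is the natural reading of discontinuation but not the only one. Randomisation follows baseline data collection, so an infant could stop before the infusion, and Table 2 marks traditional treatment through day 7.
- The larger biases need severe assumptions. A wide SAE definition takes in less lethal events, which sits badly with 80% mortality after an SAE. With 20% having an SAE and 50% to 60% mortality after it, all but one of the results (34.8%) lie within half a standard error (5 points) of 41%. The exclusion criteria may also bring trial mortality below 41%.
- A recorded death counts as an event, so listing death as a reason creates no bias unless the infant who died is dropped and replaced.
- Excess SAEs in a dose arm would still appear in the SAE counts and in the DSMB's six-monthly adverse event review. Only the mortality curve and late-event capture would be diluted.
- Mortality and late events are secondary outcomes, and the full protocol may say more.

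These points stand and limit the claim to a conditional one. They do not remove it. The article sets a rule on who may leave, lets the leaver be replaced, and does not reconcile this with outcomes that need every infant to 24 months. An analysis plan cannot recover vital status that was never collected.

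**Conclusion.** The point holds as a conflict within the protocol article with a conditional consequence. Exit and replacement after an SAE or other serious disease are permitted, and continued outcome follow-up is not secured. If infants leave and have a higher later risk of death, the 24-month Kaplan-Meier mortality is biased low, and the bias may differ by arm.

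The size cannot be fixed from the article. With an assumed true mortality of 41% at 24 months and 20% of infants having an SAE, the estimate lies between about 39% and 30% over the assumptions shown. The bias is zero if vital status is still collected, or if an SAE carries no added risk of death. The direction rests only on some infants leaving and on their later risk being higher. The sample size is unaffected.

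**What to change.** Reconcile the Withdrawal section with Table 2, Outcome evaluation, Follow-up procedures and Statistical analysis by separating two things it now merges: discontinuation of study treatment or procedures, and the end of outcome follow-up. State that:

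1. an SAE or serious disease does not by itself end outcome follow-up;
2. only death or a guardian's withdrawal of consent does;
3. all other randomised infants stay in the scheduled calls and visits for vital status and adverse events to 24 months;
4. all randomised infants are analysed in their randomised arm, whether or not a replacement was enrolled.

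No clinical stopping rule needs to change. The cost is a few sentences and some continued contact with infants who would otherwise have left, using calls and visits already in the schedule. The article reports that recruitment had not begun at submission. The wording is best settled before infants are enrolled, because follow-up that was missed may not be recoverable.

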## Background

Bronchopulmonary dysplasia (BPD) is a common chronic lung disease whose incidence is increasing annually, especially in this time of the two-child policy in China [1, 2]. Patients with BPD usually have ventilator or oxygen dependence during the early stage of the disease [3]. Most patients can gradually withdraw from the ventilator or stop oxygen treatment at different times depending on disease severity, but abnormalities in pulmonary structure and lung function may last until late childhood and even adulthood, especially in those who are diagnosed as severe BPD according to the diagnostic criteria of the National Institute of Child Health and Human Development (NICHD) [4, 5]. The mortality of overall BPD patients is about 15% [6]; nevertheless, the mortality rate of severe BPD reaches 41%, creating an enormous threat to the health of these children [4, 7]. More than 50% of survivors with BPD experience hospital readmission for repeated lower respiratory infections in the first year or two, which causes serious economic and labor burdens on families [4, 8]. Although surfactant treatment [9], prenatal steroid usage [1, 10], ventilator strategies [11], and improved nutrition [12] are used in BPD patients, effective therapies are lacking [13]. Therefore, identifying novel effective therapies for severe BPD in children is urgent and significant.

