### Sample size and calculation

The sample size of this phase-II randomized controlled trial was calculated by power analysis using the Power and Sample Size online calculator (http://powerandsamplesize.com/). The trial is designed to investigate the hypotheses of two interventions compared to control, but it is not powered to test differences between the two intervention groups. The larger of the two numbers is the sample size of this trial. The primary outcome measure is the change in the cumulative duration of oxygen therapy. The cumulative mean duration of severe BPD is reportedly 90 ± 15 days [4, 31]. This trial is powered to identify differences of 15% (from 90 days in the control group to 77 days in the low-dose groups) and 20% (from 90 days in the control group to 72 days in the high-dose groups) in participants who accept the hUC-MSC intervention. Meanwhile, the power is set at 0.8, type I error *ɑ* is 0.05, and type-II error *β* is 0.20. The calculated sample size is 21 for each group. To account for the possibility of 10% of patients being lost to follow-up, the final sample size will be 24 and the total size will be 72.

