### Randomization and blinding

Participants will be randomized into three groups in a 1:1:1 ratio after collection of the baseline data. The allocation sequence will be generated and sent to the investigators by a statistician. Participants will not be blinded during the phase-II trial and the patients in the control group will not be given hUC-MSC treatment.

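### Withdrawn infants are replaced even after randomisation, and death and SAEs are among the listed causes of discontinuation, so the rule opens a route to an outcome-selected, completers-only comparison

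*Protocol article*

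**What the plan says.** The Withdrawal section of the protocol article opens with the causes: "Discontinuation may occur due to participant death, severe adverse effects (SAEs), other serious disease-limiting participation, or study withdrawal requested by the guardian". It then says that, when a participant withdraws, "the reason for the withdrawal and all the results of observations will recorded in detail". It ends with the replacement rule: "Meanwhile, a new participant will be enrolled in the trial to replace the withdrawn subject". The rule carries no limit by reason, by arm or by time relative to randomisation, and it does not say which arm the new participant joins.

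Four other places bear on it:

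- **Randomization and blinding:** "Participants will be randomized into three groups in a 1:1:1 ratio after collection of the baseline data", and "Participants will not be blinded during the phase-II trial".
- **Sample size and calculation:** 21 per group becomes 24 (72 in total), with the reason given as "To account for the possibility of 10% of patients being lost to follow-up". The Intervention section repeats 24 per arm.
- **Outcome evaluation:** mortality is an endpoint, SAEs are a safety outcome, and death is itself counted as an SAE.
- **Statistical analysis:** mortality is compared by a chi-squared test and 24-month mortality by Kaplan-Meier curves. Oxygen duration is compared by t test.

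**The concern.** A withdrawal after randomisation can be a consequence of the assigned arm. Two of the listed causes, death and SAEs, are what the trial sets out to measure, and a third, a guardian's request, is made by a family that knows the arm. If such an infant is replaced so that the arm again holds 24, the natural bookkeeping is that the replaced infant is no longer one of the 24. An analysis of the 24 who remain would then be conditioned on events that follow randomisation.

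The arm with more withdrawals would shed its sicker infants and be refilled. Its deaths and SAEs would be under-counted, and its mean oxygen duration would look shorter than it is. Replacement also serves much the same purpose as the 10% inflation. The overlap is not an error in itself, but it means that the rule is not needed to protect power at the planned loss.

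**Working it through.** **1. The plan's own sample size.** Inputs from Sample size and calculation: control mean 90 days, SD 15, low-dose mean 77 (difference 13), high-dose mean 72 (difference 18), power 0.80, alpha 0.05. Sidedness is not stated; two-sided reproduces the figure.

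n per arm = 2 × (1.960 + 0.842)² × SD² / difference²

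- Low dose: 2 × 7.849 × 225 / 169 = 20.9, so 21.
- High dose: 2 × 7.849 × 225 / 324 = 10.9, so 11.
- Larger number 21; 21 / 0.90 = 23.3, so 24; 3 × 24 = 72.

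The stated 21, 24 and 72 reproduce.

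**2. Is replacement needed at the planned loss?** Power = Φ(13 / (15 × √(2/n)) − 1.96).

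- 21 evaluable: 13 / 4.629 = 2.808, giving Φ(0.848) = 80.2%.
- 24 evaluable: 13 / 4.330 = 3.002, giving Φ(1.042) = 85.1%.

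So 24 randomised per arm can lose three infants (3/24 = 12.5%) and keep 80% power. The planned 10% is covered without replacement.

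**3. How many are randomised if replacement continues until 72 have not withdrawn?** Expected total = 72 / (1 − q), where q is the proportion withdrawn.

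- q = 10% (the plan's loss figure): 72 / 0.90 = 80, of whom 8 are replaced.
- q = 15% (assumption): 72 / 0.85 = 84.7, about 85, of whom about 13 are replaced.

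The article gives only 72.

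**4. Bias in oxygen duration if replaced infants are left out.** Assumptions, none of them from the article: no true effect; duration Normal with mean 90 and SD 15 in every arm; log-odds of withdrawal rise by s per SD of duration, with the intercept set to give the stated withdrawal proportion; 24 kept per arm.

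- Mean among those kept = 90 + 15 × E[z(1 − p)] / E[1 − p], where z is standardised duration and p the withdrawal probability.
- Bias d = kept mean (MSC) − kept mean (control); negative favours MSC.
- Standard error = √((SD²control + SD²MSC) / 24), using the SDs among those kept.
- Type I error = Φ(−1.96 − d/SE) + 1 − Φ(1.96 − d/SE).

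| Withdrawal, control / MSC | s = 0 | s = 0.5 | s = 1 | s = 2 |
|---|---|---|---|---|
| 15% / 15% | 0 days, 5.0% | 0 days, 5.0% | 0 days, 5.0% | 0 days, 5.0% |
| 10% / 20% | 0 days, 5.0% | −0.71, 5.3% | −1.23, 6.0% | −1.78, 7.5% |
| 15% / 30% | 0 days, 5.0% | −1.05, 5.7% | −1.80, 7.3% | −2.56, 10.5% |

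Bias needs both a difference in withdrawal between arms and a link between withdrawal and duration. If every randomised infant is analysed, replacement only adds patients and this bias does not arise.

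**The case against.** The strongest reply is that the article never says replaced infants are dropped. Their observations are recorded, and the chi-squared and Kaplan-Meier analyses of mortality make sense only if deaths are kept. The analysis population is commonly defined in an analysis plan, which is not shown. This stands, and it makes the bias a conditional risk. It does not remove the point, because replacement is an enrolment rule stated in the protocol. An analysis plan could limit the damage but would leave open how many infants are randomised and where replacements are allocated.

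Second, the replacement sentence concerns the withdrawn subject, whereas death and SAEs are listed as causes of discontinuation. A reader might infer that every infant with an SAE is replaced; the text does not support that, since an SAE without withdrawal replaces nobody. Deaths are covered only if discontinuation and withdrawal mean the same thing. The section's heading and structure favour that reading without settling it.

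Third, a reader might apply the Background's 41% mortality in severe BPD, expect about 122 randomised (72 / 0.59), and conclude that mortality falls to zero in every arm by construction. The figure has no time frame, the trial excludes several high-risk conditions and also recruits infants already discharged, and the result would count replacements without measuring bias. The zero-mortality conclusion further requires that deaths be removed, which no section states.

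Fourth, it may be inferred that a replacement goes unrandomised into the vacated arm. The article does not say so; it says only that participants are randomised 1:1:1.

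**Conclusion.** The point holds as a badly fixed rule with a conditional consequence. The replacement sentence has no limit at randomisation, it stands beside causes of discontinuation that are trial outcomes, and it invites a completers-only comparison in an open-label trial of fixed size.

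If replaced infants are excluded, and withdrawal differs by arm and is related to severity, deaths and SAEs are under-counted. At an assumed 10% against 20%, oxygen duration is biased by about 0.7 to 1.8 days in favour of MSC, with type I error of about 5.3% to 7.5%. That is modest against the 13-day target. The withdrawal rates and the strength of the link to severity are assumptions. The bias is zero if all randomised infants are analysed, if withdrawal is equal across arms, or if it is unrelated to duration. It would therefore go too far to say that the randomised comparison is lost.

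One consequence does not depend on the analysis set: the number randomised (about 80 at 10% withdrawal, 85 at 15%) and the allocation of replacements are left open.

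**What to change.** In the Withdrawal section, delete replacement after randomisation, or restrict it to infants withdrawn before randomisation. Add that every randomised infant is analysed in the assigned arm and followed to 24 months unless consent is withdrawn, and that deaths and SAEs are counted in that arm. Keep the 21-to-24 inflation as the allowance for the planned 10% loss. The clinical grounds for discontinuation need not change.

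The cost is a short amendment and somewhat fewer infants with complete follow-up. Power for 13 days falls below 80% once more than three of 24 infants per arm are non-evaluable, that is, if the loss runs somewhat above the planned 10%. If 15% were expected, 21 / 0.85 = 24.7, so 25 per arm (75 in total) would be needed. Analysing every randomised infant also calls for a rule on how oxygen duration is handled in infants who die on oxygen, which the analysis plan can supply.
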